## Feasibility outcomes

Primary and secondary objectives will be assessed according to feasibility outcome measures (Table 3). Assessment of the ability to collect these data will be used to improve the design and delivery of a definitive cRCT of the TIMES intervention.

**Table 3 Tab3:** Feasibility objectives matched to feasibility outcome measures and Time-points

Feasibility objectives	Feasibility outcome measures	Time-point(s) of evaluation
Primary objective		
Objective A: the co-primary objective is to assess the (1) feasibility (% of eligible people consenting to the study) and (2) acceptability (% of intervention participants completing all three stages of the intervention) of conducting a definitive randomised controlled trial of the TIMES intervention for PLWD/MCI, and their carers, who experience problematic sleep disturbance	The proportion of eligible people who consent to participate in the study The proportion of consented participants who remain in the study and provide valid outcome data for clinical and health-economic measures, including the putative primary outcome for a definitive trial at 9- and 15-week follow-ups The acceptability of the intervention as assessed through process evaluation	Recruitment Post intervention 15-week follow-up
Secondary objectives		
Objective B: To assess the ability to collect data to address primary and secondary outcomes for the definitive RCT	The proportion of PLWD/MCI in primary care with problematic sleep disturbance (per 1000 registered patients) The proportion of PLWD/MCI in primary care, with problematic sleep disturbance and a carer (per 1000 registered patients) The proportion of PLWD/MCI in primary care, with problematic sleep disturbance and a carer who meet the eligibility criteria (per 1000 registered patients) The proportion of consented participants in the intervention arm who start the intervention The proportion of consented participants in the intervention arm who complete all three stages of the intervention The proportion of consented participants who remain in the study until final follow-up at 15 weeks The proportion of consented participants who remain in the study and provide valid outcome data for clinical and health-economic measures including the putative primary outcome for a definitive trial at 9- and 15-week follow-ups Mean and standard deviation, plus between group mean difference with 95% confidence interval and intraclass correlation coefficient (ICC) for the proposed primary outcome of the definitive trial (and any proposed outcomes that may be key secondary outcomes for which a power calculation is performed), used to verify or revise the proposed primary outcome and sample size calculation for the definitive RCT	Recruitment Recruitment Recruitment 9-week follow-up 9-week follow-up Post intervention 15-week follow-up 15-week follow-up
Objective C: To assess the ability to collect data to assess the cost effectiveness and resource use for the definitive RCT	The proportion of consented participants who remain in the study and provide valid outcome data for clinical and health-economic measures including the putative primary outcome for a definitive trial at 9- and 15-week follow-ups	9- and 15-week follow-up
Objective D: To inform iterative refinement of the TIMES intervention for the definitive RCT	The acceptability of the intervention assessed during the process evaluation	Post intervention

## Progression criteria

Criteria for determining whether to proceed to a definitive trial have been reviewed and agreed by an independent Programme Steering Committee (PSC) (Table 4). Any ambiguity in meeting the overall progression criteria will be made by the PSC in conjunction with the Funder.

**Table 4 Tab4:** Summary of progression criteria to definitive trial

	Definite Stop, i.e. abort definitive cRCT	Review required, i.e. PSC to determine progression to definitive cRCT	Definite Go i.e. proceed to definitive cRCT
Feasibility: recruitment rate	< 25% of invited eligible people consenting to participate	25–79% of eligible people consenting to participate	≥ 80% of eligible people consenting to participate
% of target sample size recruited	< 50%	50–99%	100%
Acceptability: retention to trial	< 25% of participants complete all three stages of the intervention	25–89% of intervention participants complete all three stages of the intervention	≥ 90% of intervention participants complete all three stages of the intervention
Completeness of outcome data	< 25% of participants complete key outcome data at 15-week follow-up	25–89% of participants complete key outcome data at 15-week follow-up	≥ 90% of participants complete key outcome data at 15-week follow-up
Process evaluation	Evidence that the intervention cannot be delivered with fidelity and that it is not acceptable to participants and professionals	Inconclusive evidence that the intervention can be delivered with fidelity and that it is acceptable to participants and professionals	Evidence that the intervention can be delivered with fidelity and that it is acceptable to participants and professionals

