### Co-primary objectives

#### Objective A

Co-primary objectives are to assess the (1) feasibility (% of eligible people consenting to the study) and (2) acceptability (% of intervention participants completing all three stages of the intervention) of conducting a definitive cRCT of the TIMES intervention for PLWD/MCI, and their carers, who experience sleep disturbance.

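### Table 4's row on retention to the trial scores completion of the intervention, and the only row that reflects loss from the trial names no arm

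*Protocol article*

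**What the plan says.** Table 4 (Progression criteria) has five rows. The third is headed "Acceptability: retention to trial". Its Go cell is "≥ 90% of intervention participants complete all three stages of the intervention", and its Stop cell is "< 25% of participants complete all three stages of the intervention". The Review and Go cells restrict the count to intervention participants; the Stop cell does not.

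The same quantity appears in Objective A as the definition of "acceptability (% of intervention participants completing all three stages of the intervention", and in Table 3 under Objective B as "The proportion of consented participants in the intervention arm who complete all three stages of the intervention". Table 3 lists retention as a different measure: "The proportion of consented participants who remain in the study until final follow-up at 15 weeks". The Aims and objectives section also names retention apart from completeness of outcome data and from fidelity.

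The fourth row of Table 4 concerns completeness. Its Go cell is "≥ 90% of participants complete key outcome data at 15-week follow-up" and its Stop cell is "< 25% of participants complete key outcome data at 15-week follow-up". No arm is named.

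**The concern.** The label and the count describe different things. Completing three intervention stages is adherence. Control dyads receive usual care and are not offered the stages, so they cannot contribute. A dyad that attends the review consultation and then leaves the study counts as a success on this row. A dyad that misses that consultation but gives full 15-week data counts as a failure. A report that follows Table 4 would present intervention-arm adherence as trial retention.

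That leaves completeness as the only row reflecting who stays, and as worded it does not distinguish the arms. Participants are not blinded and learn their allocation after baseline (Randomisation and blinding; Baseline and follow-up assessments). The Statistical analysis section uses observed data only, with no imputation for drop-outs. Loss that differs by arm is therefore a foreseeable problem that a feasibility trial should bring to the attention of those deciding on progression. A Definite Go on a combined percentage would not do so.

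**Working it through.** **Inputs.** 64 dyads, 32 per arm (Screening and recruitment); Go at 90% and Stop below 25% for completeness (Table 4); assumed follow-up of 80% with a 95% interval of ±10 points (Sample size calculation). Full recruitment is assumed, with each dyad counted once.

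**The plan's own figure.** 1.96 × √(0.80 × 0.20 / 64) = 0.098, or 9.8 points. The stated ±10 points is reproduced, and it is a figure for both arms together.

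**Label against measure.**

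| Place | Retention | Stage completion |
|---|---|---|
| Aims and objectives | named on its own | not named; fidelity is listed separately |
| Objective A | not defined | defines acceptability |
| Table 3, Objective B | own measure, all consented participants | own measure, intervention arm |
| Table 4 | label only, no threshold | thresholds, under the retention label |

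**What a Go on completeness allows.** 0.90 × 64 = 57.6, so at least 58 of 64 are needed and 6 may be missing. If all 6 are in one arm, that arm has 26/32 = 81.25% and the other has 32/32 = 100%, a gap of 18.75 points. The weaker arm taken alone would be in the Review band.

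**How extreme that split is.** Given exactly 6 losses unrelated to arm, the chance that all fall in the same arm is 2 × C(32,6) / C(64,6) = 0.024.

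**If loss does depend on arm.** Take assumed true completeness of 98% and 84% (illustrative values, not from the protocol), with independent participants. The combined rule returns Go with probability 0.65. Requiring at least 90% in each arm (0.90 × 32 = 28.8, so 29/32) returns Go with probability 0.22.

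**Price of reading by arm.** With true completeness of 90% in both arms and clustering ignored:
- P(at least 58 of 64) = 0.54.
- P(at least 29 of 32) = 0.60 in one arm, so 0.60² = 0.36 in both. Two arms at 29 or more always give 58 or more, so this is also the probability of meeting the combined and by-arm conditions together.

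Arm-level precision at 80% is 1.96 × √(0.80 × 0.20 / 32) = 0.139, about ±14 points.

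**The case against.** The row begins with the word acceptability, and its cells follow Objective A; only the reference to retention is misplaced. That is right: the measure itself is sound, and the error is in the label and in the Stop cell's denominator.

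A reader might go further and infer that Table 4 cannot see drop-out at all. On the stated windows the review consultation can fall as late as week 3 + 1 + 4 + 2 = 10, which leaves 5 weeks before final follow-up. The document does not support that inference. Anyone who leaves before week 15 gives no 15-week data and so counts against the completeness row. Those weeks are invisible only to the mislabelled row. For the same reason a separate retention row would add nothing at the same cut-points: retention cannot be lower than completeness, so it could never give a worse band.

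A reader might also infer that differential loss will go unnoticed. It will not. A CONSORT flow diagram will show withdrawals and losses, missing data will be reported for each outcome and time point, and the Data Monitoring Committee is unblinded and advises the Programme Steering Committee (PSC) on data completeness. What stands is narrower: none of this is tied to a progression threshold, and the PSC's discretion is written for the Review band and for ambiguity, neither of which clearly arises at 58/64.

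That the arms are combined is inferred from wording that names no arm; the unpublished full protocol may say more. The observed-data rule belongs to this trial, and the definitive trial's handling of missing data is not stated. Finally, at the planned 80% follow-up a combined Go has a probability of only about 0.018 (independent participants), so Review, where the PSC decides, is the likelier band.

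**Conclusion.** The point holds in a limited form. Table 4 mislabels a decision criterion: intervention-arm adherence carries the name of trial retention, and the denominator differs between its cells. Separately, the completeness row, on its natural reading, allows Definite Go with one arm at 81.3% and the other at 100%. That 18.75-point gap is the largest possible at the Go threshold, and it would be rare if loss were unrelated to arm. It matters because loss may well be related to arm when participants know their allocation. The size rests on full recruitment of 32 per arm and on reading the row as both arms together. Data collection is not at fault, since retention is measured and will be reported. The defect lies in how Table 4 names and applies the measures.

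**What to change.** 1. Relabel the row *Acceptability: completion of the intervention*, and use intervention participants as the denominator in the Stop, Review and Go cells.
2. Keep the overall completeness thresholds. Add that 15-week completeness, and the Table 3 measure of remaining in the study to 15 weeks, are also read by arm, and that an arm below 90% on completeness moves that row from Definite Go to Review. Masked arm labels suffice, so blinded PSC members can remain blinded.
3. Do not add a separate retention row with the same cut-points.

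This requires rewording Table 4 with the PSC's agreement and no new data. The cost is the less likely automatic Go and the wider arm-level intervals shown in the working. Because the by-arm condition leads only to Review, a chance imbalance costs a PSC discussion and cannot stop the programme.

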### Study timeline

Twenty months total: 9 months set-up; 8 months participant recruitment, trial delivery and data collection; 3 months analysis and intervention refinement.

### Risks

The TIMES intervention aims to optimise the delivery of existing elements of healthcare, including medication, but is a low-risk, non-pharmacological intervention and is hence categorised as Type A = no higher than the risk of standard medical care [90].

### Protocol date and version identifier

This manuscript was based on the final version of the study Protocol version 11 24-Feb-2025 (unpublished). Amendments to trial documents will be managed via IRAS and communicated to sites and Regional Research Development Networks (RRDNs).

### Data protection and patient confidentiality

Study data will be pseudonymised. Any data will be reported anonymously so that it will not be possible to identify any individual taking part in the study. Data will be collated, managed, stored, and processed by the UKCRC registered Exeter Clinical Trials Unit (ExeCTU), via a secure online study EDC system (REDCap Academic) [91, 92], following UK GDPR, Data Protection Act 2018, and ICH GCP E6 R2, and the secure NHS-England-validated data processing system ECLIPSE (Prescribing Services Ltd.: Company number 05913240; Data Protection Registration number Z2536678; Info Security ISO 27001; Environmental 14,001; and Quality Management ISO 9001). The trial Data Management Plan can be accessed upon request to the Sponsor.

### Dissemination plan

We aim to publish findings within 24 months of study completion, regardless of outcome, in open-access peer-reviewed scientific and clinical journals, and via presentations at local, national, and international meetings, in line with NIHR guidelines. Outcome papers will adhere to CONSORT guidelines. We will work with PPI groups to provide a lay-accessible summary of the results to all study participants. Participants will be asked to provide their contact method preferences so that they receive the results in a format of their choice.

## Roles of trial management group and independent oversight committees

### Programme steering committee (PSC)

Chair: [name], Professor of Health Services Research, University of Kent.

The PSC includes an independent chairperson with expert knowledge in the subject area, a minimum of two independent professional members, and a minimum of one independent lay representative. PSC members, excluding the Programme/Trial Manager and at least one trial statistician, will be blinded to trial arms, provide advice, and provide support and recommendations to the Funder and PMG/TMG on the overall conduct of the trial. The PSC will meet at least annually throughout the duration of the trial. The specific roles and responsibilities of the PSC are documented in the PSC charter, available upon request to the Sponsor. The PSC will act as a Trial Steering Committee (TSC).

### Data monitoring committee (DMC)

Chair: [name], Professor of Old Age Medicine (Clinical), University of Aberdeen.

The DMC includes an independent chairperson with expert knowledge in the subject area, and two independent professional members: one statistician and one clinician. DMC members will be unblinded to trial arms and provide advice, support and recommendations to the PSC on trial non-compliances, data integrity, data completeness, and safety reporting. The DMC will meet at least annually throughout the duration of the trial. The specific roles and responsibilities of the DMC are documented in the DMC charter, available upon request to the Sponsor.

#### Programme Management Group (PMG)

The PMG includes the chief investigator, programme collaborators and co-applicants, statisticians, qualitative researchers, health economists, Patient and Public Involvement (PPI) representatives, Sponsor representatives, ExeCTU data and trial management staff, and the programme/trial manager. The PMG will meet at least quarterly to monitor safety, key performance indicators and discuss and resolve emerging issues.

#### Trial management group (TMG)

The TMG includes the chief investigator, key programme collaborators and co-applicants, including statisticians, qualitative researchers, health economists, Sponsor representative, ExeCTU data and trial management staff, and the programme/trial manager. The TMG is responsible for producing the protocol, participant-facing materials and the statistical analysis plan (SAP), and will obtain relevant approvals from the relevant Research Ethics Committee (REC) and the Health Research Authority (HRA), coordinate with primary care practices to set up sites, and ensure the study is conducted according to the relevant principles of GCP and the UK Policy Framework for Health and Social Care. The TMG will meet at least monthly to manage the day-to-day running of the study and to monitor safety, key performance indicators, including trial adherence, and discuss and resolve emerging issues. Members of the TMG will analyse data, interpret analyses, report to the funder, write manuscripts for publication in peer-reviewed journals and disseminate findings at conferences and similar events.

### Indemnity

The University of Exeter, as Sponsor of the trial, holds clinical trial insurance to provide for the payment of compensation to research participants arising from injury or illness arising from the study where there is no legal liability. If an injury arises as a result of how the trial has been set up, insurance cover is provided by the University of Exeter’s clinical trials policy on a non-negligence basis. If an injury is caused by an NHS member of staff whilst carrying out any medical intervention to the participant in the study, the participant will need to pursue a claim via the NHS indemnity scheme. GP practices selected to participate in this study shall provide clinical negligence insurance cover for harm caused by their employees. A copy of the relevant insurance policy or summary shall be provided to the University of Exeter, upon request.

### End of study and post-trial care

The study will end for a participant after their 15-week assessment is complete. After this point, patient participants will continue to receive standard NHS care, with no special arrangements made in relation to the study. The patient and carer may discuss continuation of their tailored care plan with their GP, as part of their ongoing usual care, if appropriate.

## Data Availability

The dataset supporting the conclusions of this article will be made available in the University of Exeter’s Open Research Exeter repository (https://ore.exeter.ac.uk/repository/).
